#### Data Management

Study data, including survey responses and internal study tracking data, will be collected and stored in Research Electronic Data Capture (REDCap), a HIPAA-compliant web-based data management and survey distribution tool hosted at BCH [69,70]. Data transmission among BCH, AAP PROS staff, and practices will occur securely via password-protected email or fax. Paper-based data (eg, faxes and verbally administered surveys) will be stored securely for 7 years and identifiable electronic data for 3 years. Deidentified data will be kept indefinitely.

#### Data Analysis Plan

Analysts will be blinded to treatment arm. We will evaluate randomization success and level of attrition bias by comparing baseline characteristics of adolescents by treatment arm and by those retained versus those lost to follow-up (ie, adolescent participants who stop completing study surveys during the 12 months after their well visit). Baseline variables meeting a *P* value of <.20 in randomized group comparisons will be entered as control variables in multivariable modeling of the intervention effect to yield adjusted estimates of effect. We will compare rates of counseling receipt and patient ratings of their visit between groups. We will also generate variables related to intervention *dose* (eg, receipt of clinician counseling and receipt of *Contract for Life*) for use in sensitivity analyses.

To assess intervention effects on our primary and secondary outcome measures (past 90-day HED and any past 90-day riding or driving risk) at each of the 3-, 6-, 9-, and 12-month follow-up time points, we will use multiple logistic regression modeling with generalized estimating equations to compute adjusted relative risk ratios (CRAFFT-IS vs UC). Generalized estimating equations account for clustering of participants within practice and clinician. Furthermore, we will explore intervention effects on the number of days of drinking and of HED and on the number of times participants experienced alcohol-related negative consequences from baseline to each follow-up time point. As these variables are likely to have distributions that are highly skewed and overdispersed, we will specify a negative binomial distribution and log link in these regression models. We will also conduct longitudinal data analysis using mixed effects modeling to compare group outcomes trajectories through the entire 12-month follow-up period. We plan to explore intervention effect mediation by applying the product of coefficients test for mediation [71,72] and potential effect moderation by future-determined variables by testing the significance of interaction terms in regression models.

All intervention effect analyses will use intent-to-treat groups. We will transform continuous variables with skewed data and collapse categories as needed to preserve adequate cell sizes. To handle missing data, we will use multiple imputation based on regression modeling and compare the results of analyses using the imputed data set versus the original data set [73].

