### Study Design and Randomization

The study is a cluster randomized controlled trial involving 2 arms, intervention (CRAFFT-IS) and control (UC), with prospective follow-up for 12 months. Clinician randomization occurs within practice and on a rolling basis as practices enroll into the study. Participating pediatric primary care clinicians (doctor of medicine [MD], doctor of osteopathic medicine [DO], nurse practitioner [NP], and physician assistant [PA]) are randomly assigned to 1 of the study arms in a 1:1 ratio. Randomization is performed using a computerized, adaptive biased coin minimization scheme, which minimizes imbalance on the following factors, ranked by priority: clinician type (MD or DO vs NP or PA) and years in practice (≥10 vs <10) [40,41]. Compared to permuted blocks, adaptive biased coin minimization randomization has superior efficiency for achieving balance across multiple factors in studies with small units of randomization.

Clinicians are assigned a unique numeric code for temporary blinding while being randomized. After randomization, clinician study arm assignments are unblinded and shared with the study team. Study arm assignments cannot be blinded because the study team needs to train clinicians according to group assignment.

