#### Outcome Measures

A detailed listing of study outcome measures, their reference sources where applicable, and time points of data collection is presented in Table 2, and thus they are only briefly described here. These measures are also reported in the ClinicalTrials.gov registry.

Our primary outcome measure is past 90-day HED, as reported by adolescents during the 12-month follow-up period, among adolescents who report past 12-month drinking at baseline. HED is defined using the age- and sex-specific cut points recommended by the NIAAA: ≥3 drinks on a single occasion for youth assigned female at birth who are aged 14 to 17 years, ≥4 drinks for youth assigned male at birth who are aged 14 to 15 years, and ≥5 drinks for youth assigned male at birth who are aged 16 to 17 years [68]. Our secondary outcome measure is any past 90-day riding with a driver who was substance impaired (who used alcohol, cannabis, or another drug) or driving while substance impaired. The exploratory outcomes of interest include past 90-day days of use of other commonly used substances among adolescents (ie, nicotine and cannabis) and experience of negative consequences associated with alcohol use (eg, missing school or work and getting into trouble at school, home, or work). In addition, we will explore the following intermediate outcome measures as hypothesized effect mediators: (1) report of readiness to reduce or stop alcohol use using a readiness ruler [47], (2) perceived risk of harm from use, and (3) self-efficacy to refuse alcohol.

**Table 2 table2:** Adolescent participant study assessment measures by data collection time point across 12 months in the Adolescent Substance Use Prevention Intervention Research (ASPIRE) multisite cluster randomized controlled trial.

Measure					Data collection time point																								
					Eligibility survey			Previsit survey			CRAFFT-IS^a^			Postvisit survey			Monthly^b^			3 mo			6 mo			9 mo			12 mo

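### Choosing covariates by a between-arm P<.20 test would usually leave baseline heavy episodic drinking out of the effect model, at a modest cost in power

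*Protocol article*

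**What the plan says.** The Data Analysis Plan (Protocol article) checks randomization by "comparing baseline characteristics of adolescents by treatment arm". Variables that reach P<.20 "in randomized group comparisons will be entered as control variables in multivariable modeling of the intervention effect". This is the only covariate rule in the article, and no variable is named as entering regardless of the test. The same section makes adjusted relative risk ratios from logistic GEE models, at 3, 6, 9 and 12 months, the effect estimates for both the primary and secondary outcomes. It also says that the GEE handles clustering by practice and clinician.

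Under Outcome Measures: "Our primary outcome measure is past 90-day HED, as reported by adolescents during the 12-month follow-up period", in adolescents who drank in the 12 months before baseline. Table 2 shows that HED is measured by timeline followback (TLFB) at the previsit survey, so its baseline value is available for everyone enrolled. Table 2 also has a *Control variables* block (TLFB, CRAFFT, ASSIST, peer and family use, patient-clinician relationship), but does not say that these always enter a model.

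Under Study Design and Randomization: "Clinician randomization occurs within practice and on a rolling basis". Clinicians are "randomly assigned to 1 of the study arms in a 1:1 ratio" by minimization on "clinician type (MD or DO vs NP or PA) and years in practice".

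**The concern.** A between-arm test measures chance imbalance. It does not measure how well a variable predicts the outcome, or whether the randomization used it. A strong predictor that happens to be balanced is dropped, although adjusting for it would sharpen the estimate. A variable with no bearing on drinking is added if it happens to differ. The variable most exposed to this is baseline HED.

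The rule also does not say how it applies to a clinician-randomized trial. The comparison is of adolescents, so clinician type and years in practice may not be candidates at all. If they are, the article does not say whether they are tested per clinician or per adolescent.

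At stake is precision for the primary outcome in a trial whose planned power (86%) leaves only a small margin over its 80% target.

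**Working it through.** **1. The plan's own figures.** 888 / 0.70 = 1268.6, which matches the stated 1268. The 86% power cannot be reproduced directly, because no usual-care HED rate is given. Reading the 20% effect as a relative risk of 0.80, with two-sided α of 0.05 and 444 per arm, the rate that yields 86% is about 0.507. Check: p₁ = 0.8 × 0.507 = 0.406; SE = √[(0.507×0.493 + 0.406×0.594)/444] = 0.0333; z = 0.1014/0.0333 = 3.05; power = Φ(3.05 − 1.96) ≈ 0.86. The stated design effect of 0.90 implies a rate of 0.48, and a design effect of 1.17 implies 0.55. None of these rates is in the article. The simulations below assume lower rates, so only the differences between methods matter, not the power levels.

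**2. How often baseline HED enters.** With independent patients, a balanced variable passes P<.20 in 20% of trials. With 888/40 = 22.2 patients per clinician and the stated ICC of 0.008 (assumed to hold at baseline too), the design effect is 1 + 21.2 × 0.008 = 1.17. A test that ignores clustering then passes in 2[1 − Φ(1.282/√1.17)] = 2[1 − Φ(1.185)] ≈ 23.6%. Simulated frequencies agree: 19–20% without clustering, and 22–24% and 21–23% in two clustered sets. Baseline HED is thus left out in roughly 77–80% of trials.

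**3. Power at relative risk 0.80.** The strength of the baseline-to-follow-up association is assumed throughout; three values are shown per set.

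| Set | Association | P<.20 rule | Baseline HED always in | Loss (points) |
|---|---|---|---|---|
| A: no clustering | r = 0.33 / 0.50 / 0.54 | 67.6 / 70.5 / 69.7% | 70.8 / 77.4 / 77.9% | 3.2 / 6.9 / 8.2 |
| B: clustered, with minimization | OR 3 / 6 / 12 | 66.9 / 69.1 / 71.7% | 68.5 / 73.5 / 79.4% | 1.6 / 4.4 / 7.7 |
| C: clustered | OR 3 / 6 / 12 | 54 / 58 / 56% | 56 / 62 / 66% | 2 / 4 / 10 |

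- Set A: 6000 trials per scenario, modified Poisson with robust SE, assumed usual-care risk about 0.40, 828 analysed. The 828 follows from the sample-size section: the drinkers' share of eligible adolescents is 0.37/(0.37 + 0.63×0.058) = 0.910, and 1300 × 0.70 × 0.910 ≈ 828.
- Set B: 6000 trials per cell, 40 clinicians in 20 practices, 880 adolescents, ICC 0.008, logistic model with clinician-clustered SE and t(38). Assumed: usual-care risk 44%, baseline HED 40%, clinician-factor odds ratios 1.3.
- Set C: 40 clinicians, ICC 0.008, logistic model with clinician-clustered SE. Power does not rise steadily with the odds ratio, probably from simulation noise, so the 10 is the least secure end of the range.

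**4. Type I error under the rule.** Set A: 4.4 / 3.7 / 4.0%. Set B: 3.9 / 3.4 / 3.2%. Set C: 4.5 / 4.9 / 2.9%. In set B the always-adjusted test was itself slightly conservative (4.1 / 4.0 / 4.0%), so the rule accounts for only 0.2 to 0.8 points there.

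**5. The minimization factors (set B).** Tested per clinician, clinician type enters in about 1% of trials and years in practice in 1.2–1.5%, because minimization has balanced them. Tested per adolescent with clustering ignored, they enter in about 62% and 68%. Always entering both with baseline HED gave power of 73.6 / 77.6 / 83.0%, but null rejection rose to 5.3–6.1% with 40 clusters, so part of that gain is not real.

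**6. Practice indicators.** Null runs added practice, clinician type and years in practice to the model (modified Poisson, normal reference, 840 patients, ICC 0.008, 2000 runs per cell). Type I error was 20–23% with 20 practices of 2 clinicians and clinician-clustered SE, 11% with 10 practices of 4, and 7.3–7.5% with 20 practices and practice-clustered SE. A further check of the first layout gave about 20–22%. The P<.20 rule gave 3.6–5.5% in the same 2000-run cells, where the simulation standard error is √(0.05×0.95/2000) = 0.5 points.

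**The case against.** **The article does not say that nothing else enters, and the analysis plan is not shown.** This is fair as a caution: the *Control variables* block in Table 2 may reflect an intention to adjust for baseline drinking always. But the article does state an entry rule, and the block is not tied to it. If fixed adjustment was meant, the two places must be reconciled.

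**The rule is mechanical and analysts are blinded to arm.** This stands. There is little room for discretionary choice; the weakness is the criterion itself.

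**Adolescents enrol after their clinicians are randomized, so imbalance must be caught.** That argues for fixed adjustment. With 414 per arm and an assumed 40% baseline HED, gaps of up to 1.282 × √(0.4×0.6×2/414) = 4.4 points fail the test and stay uncorrected. At an assumed correlation of 0.5 such a gap moves follow-up risk by about 2.2 points, against a target difference of 8 (0.40 to 0.32).

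**The mixed-model trajectory analysis may use baseline.** The text does not say so, and that analysis does not replace the GEE models at each time point.

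**Stronger readings that the documents do not support.** A reader might infer inflated false positives; the departure is in the conservative direction. A reader might infer that practice is ignored unless the screen selects it; the GEE clustering covers practice unconditionally. A reader might infer that the minimization factors are certainly omitted; that depends on an unstated unit of testing.

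**Conclusion.** The concern holds as a loss of precision. Followed as written, the rule would omit baseline HED in about four trials out of five and cost roughly 2 to 10 points of power. The direction was the same in every scenario. The size rests on assumed baseline-to-follow-up associations and usual-care rates, and at the weak end it is small. Only baseline HED was screened in these simulations, so they approximate a rule that would screen many variables. Type I error stays at about 3–5%, so a positive result would not be made suspect by this rule. The handling of clinician type and years in practice is unclear: they enter rarely if unscreened or tested per clinician, and often, by artefact, if tested per adolescent without regard to clustering.

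**What to change.** - Delete the P<.20 screen. Prespecify the baseline value of each outcome in every effect model: baseline past-90-day HED for the primary outcome, and baseline riding or driving risk for the secondary. Add age and sex assigned at birth.
- Keep baseline tables descriptive, and move any other imbalance to a sensitivity analysis.
- Add clinician type and years in practice only together with a small-sample (few-cluster) variance correction.
- Do not add practice indicators alongside uncorrected clinician-clustered standard errors; practice is already addressed through the GEE clustering.
- State how the *Control variables* block in Table 2 relates to the effect models.

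The cost is analysis-plan wording, slightly more model specification and, if the clinician factors are used, the variance correction. Baseline drinking and riding or driving risk are already collected previsit, and the clinician factors are known from randomization. The article places data analysis after data collection ends in 2025 or 2026, so on its timeline the change can precede unblinding.

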We calculated the adolescent patient sample size by applying recruitment and retention rates, alcohol use and riding risk prevalence rates, intervention effect sizes, a within-clinician clustering design effect (0.90), and the clinician intraclass correlation coefficient for HED (0.008) seen in our pilot study [22]. We estimated a 37% past 12-month drinking prevalence rate, 28% riding risk prevalence rate among adolescents with past 12-month drinking, and a 5.8% riding risk rate among those with no past 12-month drinking. The 37% past 12-month drinking prevalence rate is similar to the 36.1% prevalence rate found on the 2018 Monitoring the Future Survey [42]. We applied slightly more conservative rates of participation (80% vs 82%) and retention (70% vs 75%) than those found in our pilot study to ensure that we achieve a sample size with sufficient power. With α set at ≤.05 and β at ≥.80, our power calculation indicated that a minimum analysis sample size of 888 participants with 12-month follow-up data would provide 86% power to detect an effect size of ≥20% in our primary outcome measure of HED. Applying the conservative estimate of 70% retention at 12 months, we need to recruit a minimum of 1268 participants. Thus, we estimate needing approximately 4200 adolescents to complete the eligibility survey, with 1600 (40% of those screened) meeting eligibility criteria, and 1300 (80% of those eligible) enrolling. To enroll this sample, we anticipate enrolling an average of 40 patients per clinician among up to 40 clinicians completing the study.

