## Results

### Recruitment and Enrollment

The first practice enrolled in August 2022. As of July 2023, a total of 6 practices (23 clinicians) had enrolled in the study.

Adolescent recruitment began in December 2022 and is expected to continue until late 2024 or early 2025. Data collection is expected to conclude in 2025 or 2026, and data analysis will follow.

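### The plan pairs a logistic GEE with adjusted relative risks but states no step from one to the other, and leaves the GEE cluster level open with at most 20 practices

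*Protocol article*

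**What the plan says.** The Data Analysis Plan names the model and the effect measure for HED and for riding or driving risk at 3, 6, 9 and 12 months in one phrase: "multiple logistic regression modeling with generalized estimating equations to compute adjusted relative risk ratios (CRAFFT-IS vs UC"). The next sentence assigns the clustering to the same method: "Generalized estimating equations account for clustering of participants within practice and clinician". Neither sentence mentions a log link, a modified Poisson model or standardization for these binary outcomes. The only link named in the section belongs to the exploratory counts (drinking days, HED days, alcohol-related consequences), for which "we will specify a negative binomial distribution and log link in these regression models".

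The sample size paragraph (Adolescents subsection) states that "888 participants with 12-month follow-up data would provide 86% power to detect an effect size of ≥20% in our primary outcome measure of HED". It gives neither the scale of that 20% nor the HED rate expected under usual care. Background and Rationale reports the earlier HED results as 22% and 34% lower risk.

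On the number of clusters, the Practices and Clinicians subsection caps enrolment at 20 practices and 40 clinicians, randomized 1:1 within practice. Recruitment and Enrollment reports: "As of July 2023, a total of 6 practices (23 clinicians) had enrolled in the study".

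**The concern.** A logit model and a relative risk do not belong together without an intermediate step. A log link is specified for the counts, so link-level detail was within the article's scope, and the binary outcomes were given the logit. An analyst who follows the text literally would exponentiate the treatment coefficient and could label it a relative risk. For a beneficial effect, the odds ratio lies further from 1 than the risk ratio, so the benefit would look larger than it is. It would also not be comparable with the earlier risk reductions that this trial sets out to replicate.

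The clustering sentence raises a second question. A GEE has one level of independent clusters. To cover both practice and clinician, the cluster has to be the practice, because clinicians are nested in it. With 20 practices or fewer, the usual sandwich variance is biased downwards and a normal reference is too optimistic.

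**Working it through.** **1. The plan's own figures.** Recruitment follows from retention: 888 / 0.70 = 1268.6, which agrees with the stated 1268. The 86% power cannot be verified, because the usual-care HED rate and the effect scale are not given. With 444 per arm and an assumed two-sided alpha of 0.05:

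- Read as a risk ratio of 0.80, power is 34%, 52%, 70% and 85% at usual-care risks of 20%, 30%, 40% and 50%. Power of 86% needs a risk of about 51%, or 48% to 55% over different ways of applying the design effect of 0.90 or the clinician ICC of 0.008.
- Read as an odds ratio of 0.80, power never exceeds about 42% under any of these variants.
- Read as a standardized effect of 0.20, power is 84.6% before any allowance for clustering.

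The stated power therefore does not fit an odds-ratio reading. It leaves two other readings open and does not establish an HED rate.

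**2. Odds ratio against risk ratio.** For usual-care risk p and a true risk ratio of 0.80, OR = [0.8p / (1 − 0.8p)] / [p / (1 − p)]. The values of p are assumptions.

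| p | Odds in intervention arm | Odds in usual care | OR | Apparent reduction |
|---|---|---|---|---|
| 10% | 0.08/0.92 | 0.10/0.90 | 0.78 | 22% |
| 20% | 0.16/0.84 | 0.20/0.80 | 0.76 | 24% |
| 30% | 0.24/0.76 | 0.30/0.70 | 0.74 | 26% |
| 40% | 0.32/0.68 | 0.40/0.60 | 0.71 | 29% |
| 50% | 0.40/0.60 | 0.50/0.50 | 0.67 | 33% |

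**3. Can a risk ratio be recovered from the logistic GEE?** A simulation with 888 participants, 40 clusters, one covariate and a true risk ratio of 0.80 gave, at usual-care risks of 20%, 40% and 50%:

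- exponentiated logistic coefficient: 0.765, 0.704 and 0.647
- risk ratio standardized from the same logistic fit: 0.804, 0.803 and 0.794
- log-link GEE: 0.804, 0.803 and 0.794

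Either route recovers the risk ratio. The bare coefficient does not.

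**4. Number of practices.** The cap is 20. Early enrolment averaged 23 / 6 = 3.8 clinicians per practice. At that rate, 40 clinicians are reached at 40 / 3.8, or about 10 practices. This extrapolates from six practices and is not a figure in the plan.

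**5. Type I error.** Null simulations used 40 clinicians, clinician ICC 0.008, about 21 to 22 analysed participants per clinician, cluster-size CV 0.5, risk 0.40 and practice ICC 0 to 0.03, with at least 5,000 trials per scenario. The nominal level is 5%. The cluster-size variation, the risk and the practice ICC are assumptions.

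| Variance and reference | 20 practices | 10 practices |
|---|---|---|
| Practice cluster, uncorrected, 1.96 | about 7% | about 10% |
| Practice cluster, Mancl-DeRouen, t on practices − 1 df | 4-5% | 4-5% |

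Uncorrected clustering by clinician gave about 2-7% over the same scenarios. The high end occurs with no practice-level correlation. The low end occurs with a practice ICC of 0.03, because arms are balanced within practice and that shared variation is then ignored.

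**The case against.** The strongest reply is that the sentence names the risk ratio as its target. Adjusted risk ratios can be computed from a logistic GEE by marginal standardization, as step 3 shows, and a condensed article may leave that step to the full analysis plan. This stands in part. A reader might infer that odds ratios will be published as relative risks and the benefit overstated by up to 33% against 20%. The article does not say so, and the table describes only what would follow if it happened. A reader might also infer that HED is known to be common here. No HED rate among drinkers is given; the figure near 50% depends on reading the 20% as a risk ratio, which the text does not settle. At a 10% risk the gap is under 2 percentage points.

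On clustering, the reply is that the article does not name practice as the cluster, an uncorrected sandwich or a normal reference. Clinicians are the randomized unit, and the only ICC quoted is theirs. That also stands, so an inflated type I error is not a demonstrated feature of the plan. Yet covering both levels in one GEE leads naturally to practice. The clinician-level alternative, left uncorrected, is not reliably at 5% either, since its error depends on a practice ICC that the article does not give.

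What the reply does not remove is that the named model and the named effect measure need a connecting step, and none is stated.

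**Conclusion.** The point holds as a mismatch to be resolved before analysis, not as a proven error in the results to come. The direct output of the named model is not the named effect measure. If the coefficient were reported as the risk ratio, a true 0.80 would read between 0.78 and 0.67 for assumed usual-care risks of 10% to 50%. This concerns the reported size of effect and its comparability with the earlier risk reductions; the hypothesis test is little affected.

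The clustering part is conditional. It applies if practice is the GEE cluster and neither a small-sample variance nor a t reference is used. In that case the error rate would be about 7% at the planned maximum of 20 practices, and about 10% if enrolment stopped near 10. Those rates rest on the simulation settings above.

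**What to change.** - **Effect measure.** Fit the binary outcomes with a log-link (modified Poisson) GEE and robust variance. Alternatively, keep the logistic GEE and state that the risk ratio is marginally standardized from it with cluster-robust intervals.
- **Clustering.** Name practice as the GEE cluster, with a Mancl-DeRouen type bias-corrected variance and a t reference on practices minus 1 degrees of freedom.

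This takes a sentence or two in the plan and a different link or option in the analysis code, with no change to data collection. The downside is slightly wider intervals. From the t reference alone, the multiplier is 2.09 with 19 degrees of freedom against 1.96 (2.09 / 1.96 = 1.07, or 7% wider). It would be 2.26 with 9 degrees of freedom (2.26 / 1.96 = 1.15, or 15% wider) if only 10 practices take part. The variance correction adds somewhat to that.
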